### Physical activity monitoring

As part of the 2-year assessment, all participants will be invited to take part in physical activity monitoring using the tri-axial accelerometer AX3 (Axivity, York, UK) to measure the impact of more frequent blood donations on activity levels. Donors who respond positively will be randomly selected to take part, with a target of 1,000 participants in each of the six sex-specific randomised intervention groups.

### Cost effectiveness analysis

A full economic analysis of alternative strategies for maintaining the supply of blood to the NHS is planned. INTERVAL trial data will be used to estimate the effect of reduced minimum inter-donation intervals on the number of blood donations made, donor’s quality of life, deferral and costs. A discrete event simulation model will be developed to extrapolate the cost effectiveness of alternative minimum donation intervals over 10 years. Data from NHSBT’s donor register (the PULSE database, Savant, Burton-in-Kendal, UK) will be accessed to provide donor characteristics and donation history to define the target population, and to estimate long-term rates of donation, under current minimum recall intervals, and characteristics of the blood collection service. Discrete choice experiments will be conducted to investigate donor willingness to donate blood under future changes to the blood collection service. The analysis will use the findings from the discrete choice experiments, together with those from the re-analyses of INTERVAL and PULSE data, to estimate the cost-effectiveness of alternative blood collection strategies over a 10-year time horizon for general populations of whole blood donors.

### Outcome measures

#### Primary outcome

The primary outcome is the number of blood donations made over 2 years. The number of blood donations up to (and not including) the 2-year anniversary date of recruitment will be counted.

#### Key secondary outcome

The key secondary outcome is physical well-being at 2 years, derived from the PCS of the SF-36v2 [21].

#### Other secondary outcomes

Other secondary outcomes, also to be assessed at 2 years, will include the following:i)The number of ‘deferrals’ of donors over the 2 years of the trial due to low haemoglobin levels and/or other factors (for example, clinical reasons, tattoos, piercings, and foreign travel).ii)Measures of iron status, including serum ferritin and reticulocyte haemoglobin.iii)Cognitive function tests of attention, executive function, intelligence, and episodic memory.iv)Physical activity measured by accelerometry.v)Cost effectiveness.vi)Donor attitudes assessed through questionnaire responses and interviews.

### Sample size

#### General considerations

The trial’s sample size was determined on the basis of partially overlapping considerations, including NHSBT's duty of care to 1.4 million blood donors per year (making it vital for the service to ascertain even subtle changes in health and well-being related to blood donation) and the need to generate sufficiently compelling evidence to influence regulators and policy-makers, since substantial benefits to the blood supply (and value for money for NHSBT) could accrue with even a comparatively small, but definite, increase in blood donation rates. As noted above, we have pre-specified interest in several subgroups because they seem *a priori* either more or less able to give blood on a more frequent basis. These donor groups are summarised in Table 4 together with their estimated prevalence based on data from previous studies [13, 29–31]. Furthermore, we will identify people in the top 20% for hereditary ‘robustness’ in relation to iron homeostasis/red cell indices by using genetic risk scores that summarise many genetic variants relevant to these traits.

**Table 4 Tab4:** **Pre-specified subgroups with suspected higher or lower susceptibility to iron deficiency following blood donation**

	Estimated prevalence in National Health Service Blood and Transplant donor population
**More resilient to deferral and iron deficiency**	
Men	47%
Carriers of the human haemochromatosis (HFE) gene variants (C282Y and H63D)	27%
Women aged >50 y	20%
Serum ferritin levels above 95^th^ percentile	5%
**Less resilient to iron deficiency**	
Body mass index <22 kg/m^2^	14%
New blood donors	10%

#### Sample size calculations related to the outcomes

This trial has been powered on its primary endpoint (number of blood donations over 2 years) and key secondary endpoint (physical component quality of life score).

(1) *Number of blood donations:* As the men in this trial are assigned to 12-wk versus 10-wk versus 8-wk inter-donation intervals, the maximum number of donations possible over the 2-year trial duration are 8, 10, and 12 donations, respectively (that is, a 25% proportional increase in donation rates when comparing a 10-wk versus 12-wk frequency, or a 50% proportional increase when comparing a 8-wk versus 12-wk frequency). Women are assigned to 16-wk versus 14-wk versus 12-wk inter-donation intervals, corresponding to a maximum number of donations over 2 years of 6, 7, and 8 respectively. However, when considering the current nonattendance rates of donors, such maximal differences based on more frequent donation intervals are unlikely to be achieved in practice.

Hence, the power calculations are based on having 80% power to detect a more realistic 5% increase in the number of donations over two years. Such an increase would be of relevance to NHSBT since it would yield an additional 70,000 units of blood per year from the same donor base. Figure 2a shows that 50,000 trial participants will provide 80% power to detect ≥5% difference in donation rates/year in subgroups with a prevalence of ≥10% (at least 5,000 donors). The sample size calculation assumes type I error = 0.05 and mean donation rate = 1.6 times/yr in the standard donation frequency group (control), and between subject SD = 0.7 times/yr in each group.

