Only participants who returned the baseline questionnaire were eligible for randomisation. After randomisation, participants were advised of their new inter-donation interval by email and were also informed that appointments should be made through NHSBT’s ISAT team. The ISAT team was responsible for making this first appointment to coincide with the participant’s allocated donation frequency. For subsequent appointments during the trial, donors are given the option, and are encouraged, to make all appointments at their selected donor centre on the occasion of future donation visits.

Once randomised, donors’ participation in the trial was flagged on their donor record together with their allocated donation frequency. This flag is critical to (1) NHSBT donor centre staff, since it is essential for the booking of future appointments at the correct interval; (2) the academic coordinating centre’s helpdesk and the ISAT team, since the flag helps to identify donors’ status on the trial and resolve any queries; and (3) data management processes, such as retrieving data on donors at regular time-points from NHSBT’s donor database and securely transferring this information to the trial coordinating centre for the purposes of monitoring appointment bookings and attendance, deferrals, adverse events of donation, positive microbiology results and deaths.

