**Figure 2 Fig2:**
[figure not shown]
**Power to detect differences in the primary and key secondary outcomes. a**: Power to detect difference in donation rates. **b**: Power to detect difference in physical component score of SF-36 survey.

(2)*Quality of life:* After making allowances for up to one third of participants not completing the final questionnaire, Figure 2b shows that 50,000 trial participants will provide 80% power to detect ≥3% mean difference in the PCS of the SF-36 in subgroups with a prevalence of ≥10%. This assumes a type I error = 0.05 and PCS = 50 in the standard donation frequency group (control), and between subject SD = 10 in each group. As a comparative benchmark, Patterson [32] showed a 3% (1.5-point) difference in the SF-36 PCS in women who self-reported iron deficiency in the past two years compared with those who had no such history.

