### Data analysis

#### Principles

Intention-to-treat analyses will be used, comparing groups as randomised. Results for men and women will be analysed separately. The principal pair-wise comparisons of groups for men will be between 10-wk and 12-wk, and between 8-wk and 12-wk intervals. For women, these comparisons will be between 14-wk and 16-wk, and between 12-wk and 16-wk intervals. For outcomes assessed at both baseline and at the 2-year follow-up, analyses of the 2-year follow-up measures will be adjusted for the baseline measures. Other baseline characteristics (age, centre, BMI and weight, SF-36v2 physical and mental component scores, haemoglobin and ferritin) will be adjusted for in secondary analyses. Tests of interaction will assess whether results differ between the subgroups pre-specified above. Multiple testing will be taken into account when interpreting these results. The trial will be reported according to CONSORT guidelines.

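### The stated 80% power for a 5% donation difference at 10% prevalence is not delivered for a mixed-sex subgroup analysed by sex: it is about 64.5% per sex

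*Protocol article*

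**What the plan says.** Under Sample size calculations related to the outcomes, the article claims "80% power to detect ≥5% difference in donation rates/year in subgroups with a prevalence of ≥10% (at least 5,000 donors"). The inputs follow: "The sample size calculation assumes type I error = 0.05", a control mean of 1.6 donations a year, and "between subject SD = 0.7 times/yr in each group". For the PCS, after allowing for loss of up to one third of final questionnaires, it claims "80% power to detect ≥3% mean difference in the PCS of the SF-36 in subgroups with a prevalence of ≥10" per cent, with a control mean of 50 and an SD of 10.

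Three other places determine how many donors enter each comparison:

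- Randomisation, concealment of allocation, and blinding: 1:1:1 allocation to three groups within each sex, which makes six groups in all.
- Data analysis, Principles: "Results for men and women will be analysed separately". Each shorter interval is compared pairwise with 12 weeks in men and with 16 weeks in women.
- End-of-trial analyses: donations are compared by t-test, and PCS by analysis of covariance on baseline PCS.

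Table 4 lists new blood donors at 10% and BMI below 22 at 14%. Neither is defined by sex.

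**The concern.** Five thousand is one tenth of all 50,000 participants, so the prevalence threshold counts men and women together. The planned comparisons do not. A subgroup containing both sexes is divided among six groups, and each pairwise test uses two of the three arms in one sex. The sample behind a test is then about half of what a three-arm reading of 5,000 donors would suggest.

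Tailoring intervals to types of donor is the second of the trial's two objectives, and new donors sit exactly at the stated threshold. A null result in them would be read against a stated 20% risk of missing a 5% difference. On the article's own inputs that risk is about 35.5% in each sex at an even split.

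**Working it through.** **Inputs.** Donations: difference 0.05 × 1.6 = 0.08 per year, SD 0.7. PCS: difference 0.03 × 50 = 1.5 points, SD 10, two thirds of donors contributing. The type I error is 0.05. The article does not say whether it is one- or two-sided, so two-sided is taken as the default. The split by sex within subgroups is not given. An even split is assumed, and alternatives are shown.

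**Formulas** (normal approximation, equal arms):

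- n per arm = 2 × (1.96 + 0.8416)² × SD² / difference²
- power = Φ(difference / (SD × √(2/n)) − 1.96)

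**Numbers needed for 80% power**

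- Donations: 2 × 7.849 × 0.49 / 0.0064 = 1,202 per arm, or 3 × 1,202 = 3,606 donors of one sex.
- PCS: 2 × 7.849 × 100 / 2.25 = 698 completers per arm.

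**The plan's own figure.** With all 5,000 spread over three arms (sexes pooled, or a single-sex subgroup), there are 1,667 per arm.

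- Donations: 0.08 / (0.7 × √(2/1,667)) = 3.30, power 91.0%.
- PCS, 1,111 completers per arm: 1.5 / (10 × √(2/1,111)) = 3.54, power 94.2%.

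The claim is met on this basis as a floor, although 80% is not reproduced as a value.

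**Sex-separate, even split.** 5,000 / 6 = 833 per arm.

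- Donations: 0.08 / (0.7 × √(2/833)) = 2.333, and Φ(0.373) = 64.5%.
- PCS, 833 × 2/3 = 556 completers: 1.5 / (10 × √(2/556)) = 2.50, and Φ(0.54) = 70.5%.

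**Other splits by sex, subgroup of 5,000**

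| Split | Donations | PCS, unadjusted |
|---|---|---|
| 47% men | 61.9% | 67.9% |
| 53% women | 67.1% | 73.0% |
| 70% in one sex (assumed) | 78.8% | 84.1% |
| 30% in the other | 43.9% | 49.1% |

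The smaller sex has at most 2,500 donors, so 64.5% and 70.5% are its ceilings.

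**What would restore PCS power at 5,000 donors, even split**

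- Baseline adjustment multiplies the SD by √(1 − ρ²). Power is 74.6% at ρ = 0.3, 79.9% at ρ = 0.45 and 82.3% at ρ = 0.5. These correlations are assumptions, since the article gives none.
- Completion: 698 / 833 = 84% completion gives 80% power with no adjustment.

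**Thresholds and detectable differences per sex, even split**

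- Donations: 6 × 1,202 = 7,212 donors, and 7,212 / 50,000 = 14.4%. At 5,000 donors the detectable difference is 2.8016 × 0.7 × √(2/833) = 0.096 per year, and 0.096 / 1.6 = 6.0%.
- PCS, unadjusted: 6 × 698 / (2/3) = 6,282 donors, or 12.6%. At 5,000 donors the detectable difference is 2.8016 × 0.60 = 1.68 points, or 3.4% of 50.

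**The case against.** Several points on the other side stand.

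- **PCS.** A reader might infer that PCS power is 70% under the planned analysis. The article does not support that. The 70.5% is for an unadjusted comparison, whereas the plan adjusts for baseline PCS, and a correlation of about 0.45 would bring power to about 80%. The one-third loss is also an upper bound. The article's stated inputs do not yield its stated PCS power per sex, but a shortfall in the planned analysis is not established.
- **Pooling.** A reader might infer that the claim can be true only with the sexes pooled. A single-sex subgroup of 5,000 also meets it, and Table 4 contains single-sex subgroups. Figures 2a and 2b are not reproduced in the text at hand, so the basis that the authors used cannot be seen.
- **Enrolled or randomised.** Because "Only participants who returned the baseline questionnaire were eligible for randomisation", a reader might infer that 50,000 overstates the number randomised. The article gives no smaller count, so no loss of power can be calculated from it.
- **Multiplicity.** A reader might want a halved type I error for the two comparisons in each sex. The stated level is 0.05, and the plan takes multiple testing into account when interpreting results.
- **Sidedness.** A one-sided 0.05 would give 75.4% for donations, still short, and 80.4% for PCS.
- **Scope.** At 27% prevalence (HFE carriers) power is 96% or more at an even or 47:53 split, and for women over 50 (20%) it is over 99%. The overall sex-specific comparisons have nearly 100%.

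None of this rescues the donations figure in a mixed-sex subgroup at the threshold, because the main donations analysis is an unadjusted t-test.

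**Conclusion.** The point holds for donations. In a mixed-sex subgroup of 5,000, the stated 80% becomes 64.5% per sex at an even split, or 61.9% for men and 67.1% for women at 47:53, and the smaller sex cannot exceed 64.5%. This rests on the article's mean, SD and effect size, a two-sided 0.05 test, and an assumed split by sex. The subgroup chiefly affected is new donors. BMI below 22 is borderline: its 7,000 donors give 78.8% at an even split, and 76.3% to 81.1% at 47:53.

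For PCS the finding is conditional. The stated unadjusted inputs give 70.5%, and the planned analysis may or may not reach 80%, depending on a correlation and a completion rate that the article does not fix.

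It would be wrong to read this as an underpowered trial. The shortfall is confined to mixed-sex subgroups near the lower end of the stated prevalence range. The statement should be corrected, but the main comparisons do not depend on it.

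**What to change.** Restate subgroup power per sex.

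- **Donations:** say that 80% power for a 5% difference needs about 3,606 donors of one sex, which is about 14.4% prevalence (7,212 donors) at an even split. Alternatively, keep the 10% threshold and state a detectable difference of 6.0% (0.096 per year).
- **PCS:** give about 12.6% prevalence (about 6,280 donors), or a 3.4% (1.68-point) difference at 10% prevalence, labelled as unadjusted with one-third loss. Alternatively, state the assumed baseline correlation and give the power of the analysis of covariance.
- State the assumed split by sex and whether the test is one- or two-sided.
- Say that these figures are for comparisons within a subgroup. They are not the power of the interaction tests under Principles. At 10% prevalence and an even split, a within-sex test of the subgroup against the remaining donors has about 60% power for an interaction of 0.08 donations per year, and about 66% for 1.5 PCS points (unadjusted).

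The cost is text only. The stated figures become less favourable, and neither recruitment, which is complete, nor the analysis has to change.

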**Figure 2 Fig2:**
[figure not shown]
**Power to detect differences in the primary and key secondary outcomes. a**: Power to detect difference in donation rates. **b**: Power to detect difference in physical component score of SF-36 survey.

(2)*Quality of life:* After making allowances for up to one third of participants not completing the final questionnaire, Figure 2b shows that 50,000 trial participants will provide 80% power to detect ≥3% mean difference in the PCS of the SF-36 in subgroups with a prevalence of ≥10%. This assumes a type I error = 0.05 and PCS = 50 in the standard donation frequency group (control), and between subject SD = 10 in each group. As a comparative benchmark, Patterson [32] showed a 3% (1.5-point) difference in the SF-36 PCS in women who self-reported iron deficiency in the past two years compared with those who had no such history.

### Data analysis

#### Principles

Intention-to-treat analyses will be used, comparing groups as randomised. Results for men and women will be analysed separately. The principal pair-wise comparisons of groups for men will be between 10-wk and 12-wk, and between 8-wk and 12-wk intervals. For women, these comparisons will be between 14-wk and 16-wk, and between 12-wk and 16-wk intervals. For outcomes assessed at both baseline and at the 2-year follow-up, analyses of the 2-year follow-up measures will be adjusted for the baseline measures. Other baseline characteristics (age, centre, BMI and weight, SF-36v2 physical and mental component scores, haemoglobin and ferritin) will be adjusted for in secondary analyses. Tests of interaction will assess whether results differ between the subgroups pre-specified above. Multiple testing will be taken into account when interpreting these results. The trial will be reported according to CONSORT guidelines.

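### The 80% subgroup power is for an arm difference within one subgroup, apparently with both sexes counted together; it does not describe the planned by-sex interaction tests

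*Protocol article*

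**What the plan says.** The protocol article's Objectives name two aims, the second being to explore tailoring of intervals to donor characteristics. The general considerations under Sample size give interest in pre-specified subgroups as one of several reasons for the trial's size.

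For donations, the sample size section claims "80% power to detect ≥5% difference in donation rates/year in subgroups with a prevalence of ≥10% (at least 5,000 donors"). The inputs follow: "The sample size calculation assumes type I error = 0.05", "mean donation rate = 1.6 times/yr in the standard donation frequency group (control") and "between subject SD = 0.7 times/yr in each group". For quality of life, after allowing for one third of final questionnaires to be missing, it claims "80% power to detect ≥3% mean difference in the PCS of the SF-36 in subgroups with a prevalence of ≥10"%, with "PCS = 50 in the standard donation frequency group (control), and between subject SD = 10 in each group".

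The Principles of the data analysis then set out the subgroup analysis: "Tests of interaction will assess whether results differ between the subgroups pre-specified above. Multiple testing will be taken into account when interpreting these results". The same paragraph has men and women analysed separately, with two pairwise comparisons against the standard interval in each sex. Allocation is 1:1:1 within sex.

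**The concern.** The power statement and the subgroup analysis concern different quantities. The first is an arm difference inside one subgroup. The second asks whether that difference departs from the one seen in other donors. Only the second bears on tailoring: a 5% gain among donors with low BMI is no reason to treat them differently if everyone gains 5%.

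The base also differs. The 5,000 donors quoted for a 10% subgroup are 10% of 50,000, so both sexes appear to be counted, while the analysis runs within each sex on about half that number.

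A reader of the results could set a non-significant interaction against the printed 80% and take it as good evidence of no difference in yield or well-being, although the planned test may have much less power.

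**Working it through.** **Inputs from the article.** Donations: control mean 1.6/yr, SD 0.7, effect 5% × 1.6 = 0.08/yr. PCS: control mean 50, SD 10, effect 3% × 50 = 1.5 points, two thirds retained. Alpha 0.05; three equal arms.

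**Assumptions.** Two-sided test; 25,000 donors per sex (23,500 and 26,500 also tried, from the 47% men in Table 4); the same prevalence in each sex unless stated.

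**Formulas.** With n_s and n_r the donors per arm in the subgroup and in the remainder:
- SE within = SD × √(2/n_s)
- SE interaction = SD × √(2/n_s + 2/n_r) = SE within / √(1 − prevalence)
- Power = Φ(effect/SE − 1.96)

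**1. The plan's own figure.** 80% power for 0.08/yr needs 2 × (0.7/0.08)² × (1.96 + 0.842)² ≈ 1,202 per arm, or 3,606 over three arms. That is 7.2% of 50,000 but 14.4% of 25,000. With 5,000 donors over three arms (1,667 per arm), SE = 0.02425, effect/SE = 3.299 and power is 91.0%. The 80% is therefore met as a floor if the sexes are pooled, but not reproduced exactly. The nearest match is 2,500 donors over two arms (81.5%), which leaves out the third arm. Figure 2 is not shown, so the sponsor's calculation cannot be checked.

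**2. Donations in one sex, 10% subgroup.** n_s = 2,500/3 = 833 and n_r = 22,500/3 = 7,500.
- Within: SE = 0.7 × √(2/833) = 0.03429; 0.08/SE = 2.333; power 64.5%.
- Interaction: SE = 0.7 × √(2/833 + 2/7,500) = 0.03615; 0.08/SE = 2.213; power 60.0%.

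**3. Other settings, alpha 0.05.**

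| Setting | Within | Interaction, same size |
|---|---|---|
| Donations, one sex, 10% | 64.5% | 60.0% |
| Donations, one sex, 14% | 78.8% | 72.6% |
| Donations, one sex, 27% | 96.9% | 90.6% |
| PCS, one sex, 10% | 70.5% | 66.0% |
| PCS, one sex, 14% | 84.1% | 78.3% |
| Donations, sexes pooled, 10% | 91.0% | 87.9% |
| PCS, sexes pooled, 10% | 94.2% | 91.8% |

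With 23,500 to 26,500 donors per sex, within-subgroup power for donations at 10% runs from 62% to 67%.

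**4. Where the loss arises (donations, 10%).** The sex split takes 91.0% to 64.5%, or 26.5 points. The move to an interaction takes a further 4.5 points (3.1 with sexes pooled; 6.2 at 14% in one sex).

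**5. Smaller interactions.** A full-size interaction means, for example, 5% in the subgroup and nothing elsewhere. At half that size (0.04/yr), power in one sex is 19.7% at 10% prevalence and 24.8% at 14%.

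**6. Multiplicity.** The article names no method. As an illustration only, Bonferroni over six factors (0.05/6) gives 33.5% at 10% and 46.9% at 14% in one sex.

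**7. Smallest interaction with 80% power, one sex, alpha 0.05.** (1.96 + 0.842) × SE interaction. For donations at 10%: 2.802 × 0.03615 = 0.101/yr, and 0.101/1.6 = 6.3%. Likewise 5.5% at 14% and 4.3% at 27%. For PCS: 1.77, 1.53 and 1.20 points.

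Table 4 gives prevalences in the whole donor population, so the share within a sex can differ. Women over 50 are 20% of donors but 20/53 = 38% of women. With 26,500 women (3,333 and 5,500 per arm), SE = 0.7 × √(2/3,333 + 2/5,500) = 0.02173, and the detectable interaction is 2.802 × 0.02173/1.6 = 3.8%.

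**The case against.** The strongest reply is that no printed figure is wrong. The article says the 80% holds in subgroups and never attributes it to an interaction. A reader might infer that the protocol promises 80% power for its interaction tests; it does not. This part of the reply stands, and the point is a mismatch between power basis and analysis, not a false interaction figure.

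It is also tempting to say that an interaction test is in itself far weaker. At these prevalences it is not. Because the standard error grows only by 1/√(1 − prevalence), a small subgroup set against a large remainder loses little, and with sexes pooled a 10% subgroup keeps 87.9%. Nor do the documents support treating 0.05/6 as the planned alpha: they mention multiple testing only in interpretation. Two of the six listed factors, sex itself and menopausal status, could not be tested within men at all. With sexes pooled, subgroups of 14% and 27% keep 83.7% and 97.7% for donations even at that alpha.

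Finally, tailoring is described as subsidiary and exploratory, subgroups are only one reason for the sample size, and an article may leave interaction power to a fuller document. That limits the consequences. It does not settle the matter, because the article does print a subgroup power, and that figure does not fit the by-sex interaction analysis it also prints.

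**Conclusion.** The point holds as a mismatch. The stated subgroup power concerns a within-subgroup difference at alpha 0.05, apparently over both sexes; the planned analysis is a by-sex interaction test. For a same-sized effect in a 10% subgroup, the planned test has about 60% power for donations and 66% for PCS; at 14%, about 73% and 78%. At 10%, most of the shortfall comes from splitting by sex and only a few points from the interaction. Half-size interactions have roughly 20 to 25% power for donations, and any formal multiplicity correction would lower all of these.

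These figures rest on two-sided tests, three equal arms, about 25,000 donors per sex and equal prevalence in both sexes. The whole-sex primary comparison is not in doubt: with 8,333 per arm, SE = 0.7 × √(2/8,333) = 0.0108, so 0.08/yr is more than seven standard errors.

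**What to change.** In the sample size section, state that the 80% refers to an arm difference within a single subgroup with both sexes counted together, after confirming this against the calculation behind Figure 2.

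Beside it, give the sensitivity of the planned test: the smallest interaction detectable with 80% power, by sex, at alpha 0.05. For donations this is about 6.3% of the control rate at 10% within-sex prevalence, 5.5% at 14% and 4.3% at 27%; for women over 50, about 3.8%. Use within-sex prevalences, not the whole-population column of Table 4, and add the PCS equivalents. If a multiplicity method is fixed elsewhere, repeat the figures at that alpha.

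In the Principles, make interaction estimates with confidence intervals the reported subgroup result.

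The cost is a short recalculation and a few lines of text. The stated subgroup sensitivity becomes less favourable. Enrolment and data collection do not change.
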